## Abstract

**Background:**

Unresectable or metastatic vulvar cancer has relatively poor outcomes despite chemotherapy-sensitized radiation therapy and combination cytotoxic therapy. Despite the virus-associated and immunogenic nature of this disease, novel immunotherapy options that exploit this advantage are currently lacking. Platinum agents such as cisplatin have been shown to prime dendritic cells for T-cell costimulation, promote downregulation of inhibitory checkpoint molecules, and sensitize tumor cells to cytotoxic T-cell killing. Radiation therapy has also been shown to promote immunogenetic cell death as monotherapy and in combination with cisplatin. In combination with pembrolizumab, cisplatin-sensitized radiation is hypothesized to increase overall response rates and recurrence-free survival in patients with vulvar cancer, via induction of an anti-tumor inflammatory response.

**Methods:**

We propose a single-arm phase II clinical trial of pembrolizumab combined with cisplatin-sensitized radiation therapy for women with unresectable, locally advanced, or metastatic vulvar cancer. The first three patients with locally advanced or unresectable disease will receive cycle 1 of pembrolizumab followed by a break and resumption of pembrolizumab at cycle 4 and as part of a safety cohort. All other patients, including the fourth patient with locally advanced/unresectable disease, will receive weekly cisplatin and pembrolizumab every 3 weeks, concurrently with daily radiation therapy. Following the completion of Cis-RT, patients will continue pembrolizumab maintenance for a total of 12 cycles. Archived tissue will be used for HPV status, MSI status, PD-L1, and TIL stratification post hoc. Imaging will be performed at baseline and every 3 cycles (21-day cycles) as per standard-of-care. Laboratory analysis will occur on the first day of each cycle.

**Discussion:**

The combination of cisplatin-sensitized radiation and immune checkpoint blockade has not been evaluated in the upfront setting for vulvar cancer. In this rare malignancy, there are limited interventional clinical trials. This trial is designed to be as accessible as possible by allowing patients to receive cisplatin and radiation locally according to accepted standard-of-care while receiving pembrolizumab and adverse event monitoring at a centralized site. A robust suite of translational correlative studies has also been built into the trial to evaluate tumor-directed immune activation.

*Trial registration* NCT04430699

## Background

Vulvar cancer represents 4% of gynecologic malignancies in the United States with an estimated incidence of 6190 women diagnosed in 2018. Of these, 20% are expected to die from disease [1]. The primary treatment for locally advanced or recurrent metastatic disease is highly-individualized, and typically involves some combination of surgery, radiation therapy (RT) with or without radiosensitization and platinum-based doublet chemotherapy [2]. Patients with locally advanced or metastatic disease at presentation have a 5-year survival of 53% and 19% respectively [3]. Patients with recurrent metastatic disease have survival rates between 14 and 15% [2]. Furthermore, no standard-of-care exists for patients who recur or relapse after primary therapy. Platinum-based combination chemotherapy for advanced or recurrent metastatic vulvar cancer has an overall response rate (ORR) of 40% [4], while single-agent paclitaxel has a response rate of 12% [5]. These have corresponded to median progression-free survival rates of 10 months [4] and 2.6 months [5] for combination and single-agent therapy respectively.

For patients with early stage disease, surgical resection with sentinel lymph node evaluation or bilateral inguinofemoral lymph node dissection is the standard. Determination of surgical margins and lymph node involvement informs the decision for re-excision or adjuvant external beam radiation (RT). Patients with lymph node involvement could also be considered for RT with or without concurrent chemotherapy with cisplatin, cisplatin plus fluorouracil (5-FU) or 5-FU plus mitomycin-C [6].

For patients with regional lymph node metastasis, extra nodal extension of the tumor, or fixed/ulcerated nodal metastasis (FIGO III/IVA), upfront surgical debulking results in significant morbidity and mortality [7, 8]. Single-agent platinum therapy is inefficacious for this disease, as illustrated by the absence of any clinical responses to cisplatin monotherapy [9]. Chemoradiation has been shown to offer significant improvements in response rate, relapse-free survival and overall survival over RT in patients with locally advanced disease [10]. As such, upfront chemoradiation has been the generally employed standard. GOG 205 evaluated the clinical response rates in patients with locally advanced squamous cell vulvar carcinoma treated with cisplatin-sensitized radiation therapy [11]. They reported a 64% response rate, allowing for many of these patients to subsequently undergo consolidative surgery. The addition of consolidative surgery after chemoradiation does not confer any significant increase in overall survival over chemoradiation alone [12]. Although the addition of chemotherapy to radiation has been shown to improve survival time to up to 44 months in patients with node-positive disease [13], there is room to increase recurrence free survival in this patient population.

### Rationale for immunotherapy and platinum-sensitized radiotherapy

Platinum agents such as cisplatin, carboplatin and oxaliplatin have long been hypothesized to promote immunogenic modulation outside of their DNA-platinum adduct formation and inhibition of DNA replication [14, 15]. Lesterhuis et al. showed that human dendritic cells exposed to cisplatin induced significantly increased T-cell proliferation [16]. Furthermore, T-cells activated by platinum-sensitized DC’s secreted increased levels of IFN-γ and IL-2 [16]. Importantly, the authors found that this effect was in-part due to down-regulation of PD-L1 and PD-L2 on DCs. Finally, they found that cisplatin-mediated STAT6 dephosphorylation led to PD-L1/2 downregulation [16]. In other reports, upregulation of mannose-6-phosphate (M6P) by cisplatin sensitized tumor cells to granzyme-B killing, and cytotoxic T-cell-medicated killing [17]. Cisplatin, has also been shown to induce immunogenic cell death via modulation of STAT signaling [18].

Ionizing radiation (RT) therapy induces IFN-γ, type I IFN production and PD-1/PD-L1 expression on tumor cells [19]. When combined with cisplatin, the immunogenic effect of RT is further potentiated via calreticulin exposure, release of ATP, induction of programmed death receptor 1-ligand (PD-L1) and high-mobility protein box-1 (HMGB-1) [20, 21]. Finally, there are several preclinical and clinical studies supporting the rational combination of immune checkpoint inhibitors with RT. For instance, combination therapy resulted in increased tumor infiltration of cytotoxic CD8 T-cells, decreased regulatory T-cells and myeloid derived suppressor cells in melanoma and glioma tumor models [22, 23]. Furthermore, combination therapy enhanced antigen-cross presentation via upregulation of major histocompatibility complex (MHC) class I (MHC-I) [24] potentially priming the immune system for checkpoint blockade.

Lastly, immunotherapy maintenance after immunogenic interventions such as local ablative therapy or radiation therapy has been shown to be beneficial. For instance, patients with non-small cell lung (NSCLC) cancer treated with maintenance pembrolizumab after ablative therapy on a phase 2 study demonstrated statistically significant improvement in progression free survival (PFS) compared to historic controls [25]. In another report by Bersanelli et al. [26], patients who revived concurrent immunotherapy with radiotherapy had a longer PFS compared to patients who received radiation alone. A randomized placebo-controlled phase 3 trial evaluated the role of maintenance durvalumab in patients with NSCLC who had received chemoradiotherapy and found significant improvements in overall response rate, 12-month PFS, 18-month PFS and duration of response [27]. Notably, these combinations were well-tolerated.

## Methods

### Aim and study design

The purpose of this study is to capitalize on the immunogenic properties of concurrent cisplatin/radiation via addition of pembrolizumab. Addition of pembrolizumab to cisplatin-sensitized radiation (Cis-RT) therapy is hypothesized to increase overall response rate, and recurrence free survival via increased cytotoxic T-cell engagement and activation. Based on this hypothesis, immunotherapy would need to be given concurrently with Cis-RT. Unlike CTLA-4 inhibitors, pembrolizumab has not been shown to have a dose-dependent relationship to toxicity with the currently utilized dose of 200 mg/m^2^ every 3 weeks. Due to this, a phase 1 trial with varying doses of pembrolizumab would not be instructive regarding toxicity and would likely impact potential efficacy. Also, due to the long half-life and frequency of administration, to test the hypothesis of synergy outlined in this study, pembrolizumab has to be present when Cis-RT is given. This makes a phase 2 trial design with pembrolizumab lead-in less ideal. In light of this, we decided to pursue a single-arm phase 2 clinical trial of concurrent Cis-RT and pembrolizumab. Finally, published and emerging toxicity data from immunotherapy plus chemoradiation combinations in other solid tumors have been reassuring, as described in the discussion section. The first three (3) patients with locally advanced or unresectable disease will receive cycle 1 of pembrolizumab followed by a break and resumption of pembrolizumab at cycle 4 and as part of a safety cohort. These patients will receive a total of 10 cycles of pembrolizumab (Fig. 1). All other patients, including the fourth patient with locally advanced/unresectable disease, will receive weekly cisplatin and pembrolizumab every 3 weeks, concurrently with daily radiation therapy (Fig. 2). Following completion of Cis-RT, patients will continue pembrolizumab maintenance for a total of 10 cycles in the safety cohort or 12 cycles for all other participants. Archived tissue will be used for MSI, PD-L1 and TIL stratification post hoc. Imaging will be performed at baseline and every 3 cycles (21-day cycles) as per standard-of-care. Laboratory analysis will occur on the first day of each cycle. We will collect and evaluate HPV status, PD-L1, and MSI status prior to therapy, but this will not be used for eligibility. Radiographic imaging will be performed every 9 weeks and overall response rate will be determined by RECIST 1.1 criteria.

**Fig. 1 Fig1:**
[figure not shown]
Treatment schema for the first three patients with unresectable disease as part of the safety cohort

**Fig. 2 Fig2:**
[figure not shown]
Treatment schema

### Patient characteristics

For this study, women ≥ 18 years with histologically or cytologically confirmed unresectable, incompletely resected, recurrent, or metastatic squamous cell carcinoma of the vulva will be eligible. Patients with unresectable disease defined as having T2 or T3 primary tumors (N0-3, M0) not amenable to surgical resection by standard radical vulvectomy will be eligible. Patients who have received prior chemotherapy, immunotherapy or radiation therapy will also be eligible. For patients who have received prior radiation therapy, re-irradiation to a previously treated site will not be permitted (Table 1).

**Table 1 Tab1:** Inclusion and exclusion criteria

Inclusion criteria	Exclusion criteria
Histologically or cytologically confirmed unresectable, incompletely resected, recurrent, or metastatic squamous cell carcinoma of the vulva. Patients with unresectable disease are defined as T2 or T3 primary tumors (N0-3, M0) not amenable to surgical resection by standard radical vulvectomy	Patients who in the opinion of the investigator cannot safely receive a minimum of 30 Gy in 10 fractions are not eligible for the trial
Participants must have measurable disease based on RECIST 1.1. Lesions situated in a previously irradiated area are considered measurable if progression has been demonstrated in such lesions	Participants who have received prior systemic anti-cancer therapy including investigational agents within 4 weeks prior to first dose of study treatment
Documented Microsatellite stability status by routine methods including MMR IHC, MSI PCR or MSI by Next Generation Sequencing (NGS)	Participants who have received a live vaccine within 30 days prior to the first dose of study drug
Participants with no prior therapy are eligible and patients with recurrent disease must not have had more than two lines of cytotoxic therapy	Participants with a history of gastrointestinal or colovesicular fistulae
ECOG performance status of 0 or 1	Has active autoimmune disease that has required systemic treatment in the past 2 years (i.e. with use of disease modifying agents, corticosteroids or immunosuppressive drugs)
Absolute neutrophil count (ANC): ≥ 1500/µL Platelets: ≥ 100,000/µL Hemoglobin: ≥ 9.0 g/dL or ≥ 5.6 mmol/L Creatinine: ≤ 1.5 × ULN AST (SGOT) and ALT (SGPT): ≤ 2.5 × ULN Total bilirubin: ≤ 1.5 × ULN	Has known active CNS metastases and/or carcinomatous meningitis

*ULM* upper limit of normal

### Study procedures

After review and signing of written informed consent and trial registration, participants will be screened for eligibility and participation in the clinical trial. Pembrolizumab may be administered up to 1 day before or after the scheduled day 1 of each cycle due to administrative reasons. Cisplatin should be given on day 1 of every cycle. At some centers, cisplatin is administered on day 3 for administrative reasons and this will be allowable on study after notification of the PI during enrollment. The first 3 patients receiving definitive chemoradiation will receive pembrolizumab on cycle 1 only and then resume on cycle 4 after completion of chemoradiation (Fig. 1). This is for the first 3 patients with locally advanced, unresectable disease only. All other patients will be treated with concurrent pembrolizumab-cisplatin-radiation throughout (Fig. 2). For logistical reasons, patients are allowed to receive standard-of-care cisplatin-radiation locally. For these patients, radiation treatment plans are to be submitted to the radiation oncologist PI. These patients must also be available for AE assessments in person on day 1 of every cycle (pembrolizumab administration days) and weekly AE assessments by telephone. All trial treatments will be administered on an outpatient basis. Radiation therapy can be administered before or after immunotherapy or chemotherapy.

Pembrolizumab 200 mg will be administered as a 30-min IV infusion every 3 weeks. Pembrolizumab will be administered first, prior to administration of cisplatin. Pembrolizumab will be continued for a total of 12 cycles, except for patients in the safety cohort who will receive a total of 10 cycles. After premedication, cisplatin 40 mg/m^2^ will be administered as a 30–60 min IV infusion (depending on institutional guidelines) weekly during radiation therapy. Cisplatin should be administered at the beginning of the week during radiation therapy. To allow for variation of administration of cisplatin at various clinical sites, cisplatin administration up to day +3 will be allowed. This request will be noted prior to patient enrollment. Cisplatin will only be administered during radiation therapy, minimum of 2 weeks, maximum of 8 weeks.

For patients with locally advanced or unresectable disease, external beam radiotherapy will be directed to the vulva and regional lymph nodes as determined by primary tumor location, including but not limited to inguinofemoral, external and internal iliac nodal regions. Treatment will adhere as closely as possible to standard of care. Any deviations will be submitted for approval to the radiation oncology PI prior to initiation of therapy. Patients with localized recurrent and/or metastatic disease with vulvar or inguinal and/or pelvic involvement and no prior history of radiation therapy are also candidates for tumor-directed radiotherapy to the site of recurrence. Patients with recurrent metastatic disease and a history of prior radiation can be considered if the target lesions are outside the prior radiation field, symptomatic, or if in the opinion of the investigator the patient can safely receive and benefit from additional radiation. CT simulation is required to define the gross tumor volume (GTV), clinical target volume (CTV), and planning target volume (PTV). The CT scan must be acquired in the same position and immobilization device as for treatment. The vulvar GTV and the groin GTV when inguinal nodes are unresectable will receive 68–70 Gy in 32–38 fractions of 1.8–2.2 Gy per fraction, provided organs at risk (OAR) metrics are met. Dose painting is permitted. Treatment will be delivered once daily, 5 days per week for the treatment duration. Breaks from treatment should be minimized and reasons for breaks must be documented. The groin PTV when high-risk positive nodal features are present after lymph-node dissection will receive 60 Gy in 30 fractions. Uninvolved pelvic or inguinal nodes should receive 45–50.4 Gy. Patients with unresectable/unresected pelvic nodes will receive radiation to a dose of 64 Gy, as OARs allow. For patients with a prior history of radiation, no overlap of previously treated sites will be permitted. Thoracic metastasis will not to be irradiated. Treatment of bone metastases are allowed. Patients who in the opinion of the investigator cannot safely receive a minimum of 30 Gy in 10 fractions for metastatic disease are not eligible for the trial.

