### Statistical considerations

The target enrolment is 24 patients. The primary endpoint for this study is overall response rate (ORR). This sample size calculation is based on an ORR of ≥ 60%. For recurrent metastatic disease, there are is no standard of care. The ORR estimation is informed by data showing an ORR of 40% in patients with advanced or recurrent metastatic vulvar cancer treated with platinum-based combination therapy [4]. Single-agent chemotherapy has an ORR of about 12% [5]. Patients with primary disease who are not candidates for upfront surgery have a reported response rates from 55% [30] to 64% [11]. Only patients who undergo treatment on protocol will be eligible for analysis. Patients who sign consent and do not undergo any treatment will be ineligible for evaluation. With n = 24, the power to reject Ho: ORR ≤ 30% in favor of H1: ORR ≥ 60% will be 89% at a target significance level of 0.05 for a one-sided exact Binomial test (12 or more responses are required to reject Ho in favor of H1). Six-month Recurrence Free Survival (RFS-6) is the secondary endpoint. Exploratory biomarkers include; Predictive values of baseline dMMR/MSI-status and PD-L1; Anti-tumor inflammatory responses of cGas-STING- pathway, systemic inflammatory cytokines, and circulating T-cell receptor repertoire.

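### The radiotherapy text gives lesions inside a prior radiation field a route to on-study radiation that the protocol elsewhere bars without exception

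*Protocol article*

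**What the plan says.** Four places in the protocol article bear on the point.

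- **Study procedures, radiotherapy text, permissive sentence.** "Patients with recurrent metastatic disease and a history of prior radiation can be considered" on any of three grounds: "if the target lesions are outside the prior radiation field, symptomatic, or if in the opinion of the investigator the patient can safely receive". The sentence then adds that the patient should also be expected to benefit from the further radiation.
- **Study procedures, later in the same text.** "For patients with a prior history of radiation, no overlap of previously treated sites will be permitted". No exception is given.
- **Patient characteristics.** "For patients who have received prior radiation therapy, re-irradiation to a previously treated site will not be permitted". Again there is no exception, and the sentence refers the reader to Table 1.
- **Table 1.** No criterion on re-irradiation appears. The nearest entries are an exclusion for patients whom the investigator judges unable to receive safely at least 30 Gy in 10 fractions, which does not mention prior fields, and a measurability sentence: "Lesions situated in a previously irradiated area are considered measurable if progression has been demonstrated in such lesions".

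**The concern.** The permissive sentence and the two bans give different answers for the same lesion. If the grounds in the permissive sentence are true alternatives, a symptomatic lesion inside the old field, or a favourable judgement by the investigator, is enough for the patient to be considered. If the bans govern, that lesion can never be irradiated on study, and the second and third grounds add nothing for it.

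Two things are at stake: who is enrolled, and whether a previously treated site is irradiated again. Study procedures lets patients receive cisplatin and radiation locally, so teams outside the central site also have to apply this text. Two teams acting in good faith could decide opposite ways.

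**Working it through.** **Design figures, for context.** The point contains no figure of its own, but the plan's calculation was reproduced to see whether anything depends on it. Inputs from Statistical considerations: n = 24, null ORR 30%, alternative ORR 60%, one-sided exact binomial test at 0.05, rejection at 12 or more responses, stated power 89%.

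Formula: P(X ≥ r) = Σ from k = r to 24 of C(24, k) p^k (1 − p)^(24 − k).

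| Cut-off r | Type I error at p = 0.30 | Power at p = 0.60 |
|---|---|---|
| 11 | 0.0742 | 0.9465 |
| 12 | 0.0314 | 0.8857 |

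The stated 89% is reproduced, and 12 is the smallest cut-off that keeps the error below 0.05. None of these inputs depends on the re-irradiation rule, so settling that rule changes none of them.

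**The rules side by side.** Classify a target lesion in a previously irradiated patient with recurrent metastatic disease by three yes/no facts: inside the old field, symptomatic, and judged by the investigator safe and worthwhile to irradiate. That gives 2 × 2 × 2 = 8 combinations.

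| Lesion | Permissive sentence | Two bans |
|---|---|---|
| Outside the field (4 combinations) | can be considered | may be irradiated |
| Inside, neither symptomatic nor favourably judged (1) | no route | barred |
| Inside, symptomatic only (1) | can be considered | barred |
| Inside, favourably judged only (1) | can be considered | barred |
| Inside, both (1) | can be considered | barred |

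The rules agree in 4 + 1 = 5 combinations and conflict in 3, all of them in-field. These are logical cases, not shares of patients.

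**Does another parsing remove the conflict?** The comma before the word for symptomatic could be read as joining the first two grounds, so that a lesion must be both outside the field and symptomatic, with the investigator's judgement as the alternative. The judgement route alone still reaches in-field lesions, in 2 of the 8 combinations (symptomatic or not). The conflict becomes smaller but remains.

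**Does Table 1 settle it?** No. It is the place cited for the ban but does not contain it. Its minimum-dose exclusion depends on the investigator's view of safety and does not refer to earlier fields.

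**The case against.** The best defence is that candidacy and delivery are separate steps. The permissive sentence says only that patients may be considered. It never states that a treated site may be irradiated again. The ban is categorical and appears twice, once later in the same text. On that reading a patient may enter on any of the three grounds, and her radiation is then confined to untreated sites. There are also checks: plans for locally treated patients go to the radiation oncology lead, and the text on locally advanced disease requires approval of deviations before treatment starts.

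Part of this stands. The protocol does not expressly authorise overlap, and plan review lowers the chance that overlap would happen unnoticed. But the first two grounds describe the target lesions themselves, and the third is about receiving further radiation. If in-field lesions can never be irradiated, the text does not say what the second and third grounds are for, and a site could fairly read them as exceptions. Whoever reviews the plan works from the same conflicting sentences.

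A reader might also infer a problem with the primary endpoint: Table 1 counts a progressing in-field lesion as measurable, the bans leave it unirradiated, and the patient is still scored for ORR. The documents do not support pressing this.

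- The Table 1 sentence defines which lesions may be measured under RECIST, not which are irradiated, so it contradicts neither ban.
- The protocol already accepts unirradiated disease: metastatic patients are eligible, yet thoracic metastases are not irradiated. The Discussion also looks for a systemic anti-tumour response.
- The 30 Gy in 10 fractions exclusion may remove a patient with no site left to irradiate, although it is worded around safety and so does not settle the matter.

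**Conclusion.** The contradiction is real and should be corrected. The permissive sentence in Study procedures treats lying outside the old field as one ground among several, while the later sentence there and the one in Patient characteristics make it a condition with no exception. Table 1 does not decide between them.

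The scope is narrow. The permissive sentence covers only recurrent metastatic disease with prior radiation, and the rules diverge only when target lesions lie in the old field. Patients whose target lesions are all outside it satisfy both rules, so it would be wrong to say that every recurrent patient with prior radiation is affected. The protocol does not say how many patients fall in the affected group, and no estimate is offered here.

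The effect is on eligibility and radiation exposure. The sample size, cut-off, type I error and power are untouched. One patient is 1/24 = 4.2 percentage points of the ORR, but that is the weight of any single patient and shows neither the direction nor the size of a bias.

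The conclusion assumes that the article's wording matches what sites are given. A fuller protocol, not shown here, might already resolve the conflict, but the published sentences would still disagree.

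**What to change.** Reconcile the two sentences in Study procedures, the sentence in Patient characteristics and the eligibility list in Table 1 into one rule for patients with prior radiation. The rule should state whether the symptomatic and investigator-judgement grounds can override the no-overlap rule. If they cannot, it should say what those grounds add for a patient who already has to meet it. The same wording should stand in Table 1, since Patient characteristics cites it. Which rule applies is a clinical decision for the sponsor, and this review takes no position on it.

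The cost is a wording change, circulated to the local teams that deliver radiation. The Table 1 measurability sentence need not be tied to the irradiated sites, and the sample size and analysis need no change.
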